### Demographic and clinical assessments

At baseline, we will collect information on participant’s age, gender, smoking status, years of education, cause of the SCI, date of the SCI, drug/alcohol use, body mass index (BMI), medical history such as diabetes mellitus or hemodynamic regulation problems (hypertension, hypotension, autonomic dysreflexia) or respiratory problems (nocturnal apnea or use of a device for sleep apnea, signs of restricted or obstructive lung disease on spirometry test) or history of intensive care admission, medication use, history of TBI, and infections or wounds in the past 3 weeks. Some clinical tests will also be conducted upon baseline, while others are also measured at follow-up since we expect they may change due to our intervention. The latter are therefore seen as secondary outcomes and may be evaluated in a separate study.

The following clinical tests will be conducted:

At measurement timepoint 1SCI classification: Functional impairment in terms of sensation and strength of key muscles will be assessed using the AIS classification [39]. It is a structured clinical assessment of the level and completeness of the spinal cord injury. Intra- and interobserver correlation coefficients are generally around 0.9 [44].Lung spirometry: A portable spirometer (Vitalograph In2itive) will be used to assess forced expiratory volume in one second (FEV1), forced vital capacity (FVC) and peak cough flow (PCF) (L/s).Heart rate and blood pressure measurement using an automated device will be measured at the left or right arm in seated position.

At measurement timepoint 1 and 4Spasticity level: The Perceived Resistance to Passive Movement (PRPM) test is recommended by the Dutch guidelines for measuring spinal spasticity [45]. The scale ranges from (0) ‘no increased resistance’ to (4) ‘movement of the limb impossible’. Resistance of elbow flexors, elbow extensors, wrist flexors, wrist extensors, hip adductors, knee flexors, knee extensors, ankle plantar flexors (both with extended and with a 90° flexed knee) will be assessed in supine position. A sum of the scores will be used as the outcome measure, ranging from 0 to 32.Electrically-evoked muscle strength: The MicroFET2 (Hoggan Scientific, LLC) muscle strength testing system is an handheld dynamometer, which will be used to measure electrical stimulation-evoked quadriceps force. The electrical stimulation protocol will be equal to that used during the 12 week intervention. The dynamometer will be affixed to a band, which in turn will be secured around the wheelchair and the distal part of the participant's lower leg. The MicroFET2 dynamometer demonstrates a high intra-rater reliability for knee extension, with an interclass correlation coefficient (ICC) of 0.93, a standard error of measurement (SEM) of 17.2N and a minimal detectable change of 47.5N [46].

The following questionnaires will be used:

At measurement timepoint 1Brief Physical Activity Assessment Tool: This tool is a two question physical assessment. It has a validity similar to that of more detailed self-report measures of physical activity. It can be used efficiently in routine primary healthcare services to identify insufficiently active patients who may need physical activity advice [47].TBI-4 questionnaire: This questionnaire is specifically designed as a self-report tool to determine the likelihood of TBI in traumatic SCI patients utilizing just two questions. The outcome is presented as improbable TBI, possible TBI, mild TBI, moderate TBI or severe TBI. At the cut-off “possible TBI” this tool had a sensitivity of 83% and a specificity of 51% to detect mild TBI based on medical reports, indicating this questionnaire can be used as a guide in the unavailability of medical reports, but should be interpreted with care [48].

At measurement timepoints 2 till 5Cognitive Failures Index: This test can reliably evaluate how participants experience their own cognitive function. It consists of 25 questions, each scored on a 5-point scale ranging from never (0) to very often (5) [49].McGill Pain Questionnaire: Participants will be given a figure of a person, where they can color the zone of pain. They will be asked to describe the pain and score it on a 10 point visual analogue scale (VAS) and will receive some questions related to the impact of pain on their daily life [50].Hospital Anxiety and Depression Scale (HADS): this scale is a widely used and reliable screening instrument to assess the severity of anxiety and depression [51]. A subtest score of more than 8 on 21 denotes considerable symptoms of anxiety or depression.Fatigue Severity Scale: This questionnaire encompasses nine questions and has previously been used to recognize and diagnose fatigue in patients with neurological disorders [52].Pittsburgh Sleep Quality Index: This index consists of 19 questions concerning seven domains related to sleep quality in the preceding month. Every domain receives a score of 0–3, with a total score of 0–21. A score of more than 5 indicates a poor sleep quality [53].Utrecht Scale for Evaluation of Rehabilitation – Participation (USER-P): This test is widely used to assess participation in daily life activities in rehabilitation contexts. It contains 32 questions related to the frequency of participation, participation restrictions and satisfaction with participation, with a total score of 0–100 for each of these three domains. A higher score indicates a better participation [54].

The baseline measurements of potential moderators of the effect of our intervention on cognitive and blood outcomes and risk factors for cognitive impairments according to a previous review paper will be entered in the statistical analysis [4]. The risk factors for cognitive impairments will be entered as a combined risk score with a maximum score of 10, indicating the highest risk. Participants receive a score between zero and one for each of the following: 1 point if self-reported history of TBI or mild to severe concomitant TBI according to TBI4 questionnaire [48], 0.5 points for a score of > 8/21 for anxiety and 0.5 points for a score of > 8/21 for depression on the HADS scale [51], 1 point for chronic pain indicated on the McGill pain questionnaire to exist longer than 3 months and is scored at its minimum a VAS score of 3 [50], 0.5 points for a history of autonomic dysreflexia and 0.5 points for a blood pressure below 90/60 upon measurement, 1 point for tetraplegic participants compared to 0 points for paraplegic participants, 0.33 points for self-reported sleep apnea, 0.33 points for a FVC value below 0.85% of the predicted value, and 0.33 points for a PCF below 4.5L/s, 0.25 points for regular alcohol use (more than once per week), 0.25 points for drug abuse, 0.25 points for polypharmacy (more than 7 prescribed drugs), 0.25 points for any medication acting on the central nervous system, 1 point for participants who finished only basic education, 0.5 points for participants who finished only secondary education, 0.5 points for diabetes mellitus, 0.5 points for a BMI equal to or above 25 kg/m^2^ [55], 1 point for previous intensive care admission.

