### Study design and procedures

#### Study design

This study will apply a randomized replicated sequential ABC single-case experimental design (SCED), with a baseline (A), intervention (B) and follow-up (C) phase [36, 40]. SCED study designs demonstrate strong internal validity to determine the likelihood of a causal relationship between the intervention and outcomes. One entity is observed repeatedly over a certain time period under different levels of at least one independent variable. The power in SCEDs is related to the number of data points for each participant and not the number of participants. Each participant serves as his/her own comparison, thus controlling for confounding variables that can impact outcome and allowing heterogeneous clinical presentations. The internal validity of the SCED results can be improved by randomization techniques such as randomization of the starting time of the intervention. The downside is that the generalizability of the study results to the total population still depends on the number of participants included (i.e. replication of the findings) [40, 41]. The SCED lend itself perfectly to reflect on the reasons for the (likely) variability in the onset of NMES-induced effects on cognitive performance, looking at individual participant’s intervention courses. Thus, allowing to reflect on the existence of different potentially moderating characteristics. Several potential moderators have been suggested previously [4] and will be measured within this study. These include concomitant traumatic brain injury, psychological alterations, chronic pain, hemodynamic dysregulation, level of injury, respiratory failure, substance (ab)use, educational level, cardiovascular diseases, and intensive care admission [4]. In addition, a SCED design allows us to interpret after how many weeks the NMES leads to changes in performance on the momentary digital symbol substitution task. The aforementioned advantages of SCED studies indicate how this design offers additional information that is well fitted for an explorative study in a new topic.

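### The FVC component of the combined risk score has a cut-off (0.85% of predicted) that no participant can meet, so as written it always scores zero

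*Protocol article*

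**What the plan says.** The section Demographic and clinical assessments of the Protocol article defines a "combined risk score with a maximum score of 10, indicating the highest risk". It adds: "Participants receive a score between zero and one for each of the following". Respiratory problems are scored through three components of equal weight:

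- "0.33 points for self-reported sleep apnea"
- "0.33 points for a FVC value below 0.85% of the predicted value"
- "0.33 points for a PCF below 4.5L/s"

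The two lung-function values come from the portable spirometer used at T1, which gives FEV1, "forced vital capacity (FVC) and peak cough flow (PCF) (L/s"). No other place in the article restates the FVC cut-off.

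The Study design section names ten potential moderators, ending with "level of injury, respiratory failure, substance (ab)use, educational level, cardiovascular diseases, and intensive care admission". The ten domains of the score correspond to that list.

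The same assessment section describes the 25 items of the Cognitive Failures Index as "each scored on a 5-point scale ranging from never (0) to very often (5"). This questionnaire is given at T2 to T5 and is not part of the risk score.

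**The concern.** A threshold of 0.85% of predicted is roughly one hundredth of the lung volume expected in a healthy person of the same build. A scoring rule that nobody can satisfy carries no information: the component is a constant zero, and a participant with clearly restricted lung function scores the same on it as one with normal function.

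The loss is not a uniform shift of the score. It falls only on participants whose FVC is reduced, so it can change how participants rank on a variable meant to help explain why they respond differently. Reduced FVC is plausible in this sample, because the trial admits injuries at L2 or higher and the score itself separates tetraplegic from paraplegic participants. With 15 participants in a study where neither they nor the researchers are blinded to phase, a scoring threshold should be settled before outcomes are seen, not repaired when the score is computed.

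The Cognitive Failures Index raises a similar but separate question. Consecutive codes from 0 to 5 make six categories, not five.

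**Working it through.** **Inputs.** All weights are from Demographic and clinical assessments in the Protocol article. Basic education (1 point) and secondary education only (0.5) are taken as mutually exclusive, so education contributes at most 1. The grouping into ten domains follows the moderator list in Study design.

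**Step 1: reproduce the stated maximum of 10.**

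| Domain | Weights | Maximum |
|---|---|---|
| Traumatic brain injury | 1 | 1.00 |
| Anxiety, depression (HADS) | 0.5 + 0.5 | 1.00 |
| Chronic pain | 1 | 1.00 |
| Autonomic dysreflexia, low blood pressure | 0.5 + 0.5 | 1.00 |
| Tetraplegia | 1 | 1.00 |
| Respiratory (apnea, FVC, PCF) | 3 × 0.33 | 0.99 |
| Alcohol, drugs, polypharmacy, CNS medication | 4 × 0.25 | 1.00 |
| Education | 1 | 1.00 |
| Diabetes, BMI | 0.5 + 0.5 | 1.00 |
| Intensive care admission | 1 | 1.00 |

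Sum: 9 × 1.00 + 0.99 = 9.99. This reproduces the stated 10. The missing 0.01 is the rounding of one third to 0.33 and is not an error. The maximum is reached only if the FVC component can be scored.

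**Step 2: can the printed cut-off be met?** The article gives no predicted FVC values, so I assume a range of 2 to 6 L.

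| Predicted FVC (assumed) | 0.85% of predicted (as printed) | 0.85 of predicted (as a ratio) |
|---|---|---|
| 2 L | 2 × 0.0085 = 0.017 L (17 mL) | 1.70 L |
| 4 L | 4 × 0.0085 = 0.034 L (34 mL) | 3.40 L |
| 6 L | 6 × 0.0085 = 0.051 L (51 mL) | 5.10 L |

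Across the assumed range the printed cut-off is 17 to 51 mL, which no participant able to do the test would fall below. The same figure read as a ratio gives 1.7 to 5.1 L, which can separate participants.

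**Step 3: effect on the score if the text is applied literally.**

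- Respiratory domain maximum: 0.99 − 0.33 = 0.66.
- Total maximum: 9.99 − 0.33 = 9.66.
- For one participant, if 85% was meant: anyone with FVC from 0.85% up to just under 85% of predicted loses 0.33. Everyone else loses nothing.
- Share of the whole scale: 0.33 / 9.99 = 3.3%. Share of the respiratory domain: 0.33 / 0.99 = one third.

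**Step 4: where the score does not enter.** The primary test statistic is the difference between phase means of the smartphone test within a participant. The SCED reasoning on sample size rests on the number of possible phase-change points, and the G*Power calculation on an effect size and a correlation among repeated measures. None of these uses the risk score.

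**Step 5: Cognitive Failures Index, 25 items.**

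- Codes 0 to 4 (five codes): total 0 to 100.
- Codes 1 to 5 (five codes): total 25 to 125.
- Codes 0 to 5 (six codes): total 0 to 125.

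Either of the first two fits a 5-point scale. The article does not show which end is misprinted.

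**The case against.** The strongest reply is that this is a visible unit slip. Anyone scoring the data would probably notice that the cut-off is unworkable, and nothing in the article shows that the literal text will be followed. Raw FVC is recorded at T1, so the component can be recomputed at any time. The effect is bounded at 0.33 of about 10 points. The secondary test named in the article, the Friedman test, takes no covariate, so no specific result can be shown to change.

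Most of this stands, and it limits the weight of the point. It does not remove the error. The printed figure is an operational threshold, it conflicts with the score's own stated maximum, and the article says the score will be entered in the analysis. Noticing the slip later still leaves someone to choose the replacement value at that stage.

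A reader might infer several stronger things that the article does not support:

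- *That the whole respiratory item is always zero.* Only the FVC component is. Sleep apnea and PCF can still give up to 0.66, and the spirometry still contributes through PCF.
- *That everyone with restricted lung function is classed as having no respiratory risk.* Such participants may still score on PCF or apnea.
- *That the moderator score is certain to be wrong.* This follows only if the text is applied literally.
- *That the Cognitive Failures Index must be coded 0 to 4, or that a comparison with norms is at risk.* Codes 1 to 5 fit the description equally well, the article plans no comparison with norms, and the index is not part of the risk score.

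**Conclusion.** The point holds for the FVC component alone. As printed, its cut-off cannot be met. Applied literally, it fixes that component at zero and limits the total to 9.66 against a stated maximum of 10. Participants with reduced FVC would be under-scored by up to 0.33 points, about 3.3% of the scale, wherever the score is used as a moderator. The primary randomization test and the sample size are untouched.

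That the cut-off cannot be met rests on the assumed predicted FVC of 2 to 6 L, but the margin is so wide that no realistic value would change it. That 85% was meant is an inference: it is the natural reading of 0.85, but the article does not say so.

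This is a small correction, worth making because it concerns a working rule for a planned analysis. The Cognitive Failures Index range is a separate, minor inconsistency that the article alone cannot resolve.

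**What to change.** 1. Have the sponsor confirm the intended FVC scoring threshold, presumably 0.85 of predicted, i.e. 85%. Correct the unit in the score definition and in any scoring script before the score is computed, and record the date of the correction.
2. Derive the component from the FVC measured at T1. No new measurement is needed, and the stated maximum of 10 (9.99 with rounded thirds) is then attainable.
3. Reconcile the Cognitive Failures Index code range with the form actually used, and apply the same codes at T2 to T5.

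The cost is two corrected lines of text and a check of the scoring script. Design, schedule, sample size and primary analysis do not change.

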### Statistical analysis

#### Single-case data

For our primary aim, the smartphone cognitive assessment, statistical analysis will be performed using the Shiny app for Single-Case Data Analysis (Shiny SCDA) [56]. A total of 54–69 measurements per participant will be attained.

##### Visual analysis

First, measurement points will be plotted and visually inspected per participant. Six features will be visually examined according to the guidelines of Lane and Gast (2014): cognitive performance in the different phases, variability in cognitive performance both within and between phases, trends in the data, immediacy of effect, overlap of data points between phases, and consistency of data patterns across participants [57]. Instead of inspecting only immediate effects, also the existence of a potential delay of the effect and consistency of this delay between participants will be explored [58].

##### Effect size measures

Finally, effect size measures will be calculated for each participant. This will be done by calculating the percentage of non-overlapping pairs between phases [59]. The NAP (Nonoverlap of All Pairs) value equals the number of comparison pairs showing no overlap, divided by the total number of comparisons, and can be considered an area under the curve percentage from a receiver operating characteristic analysis [60].

##### Randomization test

Subsequently, randomization tests will be performed to test the null hypothesis that NMES does not have an effect on participant’s cognitive function. The observations of the baseline phase will be compared to those of the intervention and follow-up phases respectively. The test statistic “means of phase A minus means of phase B” will be chosen as the primary outcome of this study. In case visual analysis suggests delayed effects, the randomization test will be repeated with lagged data until the lowest p-value has been reached (one effect lag equals one day). The first 4 measurements in the baseline phase will be removed before calculating the means, since we expect a learning effect on the first trials, leaving between 5 and 20 measurement points depending on the randomly decided length of the baseline period. Studies that tested the statistical properties of a randomization test used in this type of design showed that the Type I error probability of the randomization test was maintained at an acceptable level [61].

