In the context of SCED studies, randomization does not refer to individuals being randomly allocated to treatment groups, but to the random onset of the intervention phase which is usually set within a fixed window of time in order to make this randomization more feasible [38]. In this study, a window of 9 to 24 measurement points (i.e. 3 to 8 weeks at the set frequency of three test assessments per week) will be employed in which the change of phase from baseline to intervention phase will be randomly determined. This determination will be done with a random number generator in Excel set to give a random number between 9 and 24. There will be a baseline phase ranging from 3 to 8 weeks, followed by an intervention phase of 12 weeks and a final follow-up phase of 3 weeks after a 12 week rest period with no measurements and no interventions. As we will exclude the first 4 measurements in the baseline phase from analysis, see Sect. "Statistical analysis", this leaves us at least 5 measurement points in this phase, 36 measurement points in the intervention phase and 9 measurement points in the follow-up phase. Neither participants nor researchers will be blinded to the phase of the intervention. Replication of the experiment will be done in 15 participants.

Finally, additional measurements will be done in a repeated manner according to a single-armed prospective design before baseline phase, at the end of the baseline phase, at the end of the intervention phase and at the start of the follow-up phase.

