### Cognitive assessments

#### Smartphone-based cognitive assessment

To study the primary aim of our study, participants will undergo a cognitive test for 3 times a week during the baseline, intervention and follow-up phase of the experiment. This repetitive cognitive test will be administered using a secured smartphone application, which was designed for use in clinical settings and research (m-Path, https://m-path.io/landing/). It will be programmed to emit an auditory signal three times a week signaling the availability of a new cognitive test between 7.30 AM and 10.30 PM on the days that participants do not undergo NMES sessions. The test is the momentary digital symbol substitution task, which is a measure of processing speed and short-term working memory function. For this test, participants have 30 s time to complete as many trials as possible where they need to correctly select the figure representing the number given as depicted in the legend provided on the top of the screen. The outcome is presented as response time derived from the number of trials/30 s (speed, in ms) and the percentage of correct trials (accuracy). Before the test starts, participants will be informed that they should be ready to respond as fast and accurate as possible. Daniëls et al. (2020) have validated this test for repeated use in healthy adults. They reported a significant learning effect for number of correct answers in 30 s between the first and 48th trial (B = 0.32, SE = 0.04, *p* < 0.001; with number of correct answers as the dependent variable and the logarithmic transformation of the session number (between 1 and 48) as the independent variable) [42].

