##### Secondary statistics

Before analysis, the data will be checked for outliers, defined as values lying further than three times the interquartile range away from the median value. The normality assumption will be checked based on visual representations of the data using histograms and measurements of skewness and kurtosis (normality assumed if the data values lie between -2 and + 2) [64]. Homoskedasticity will be tested using the Levene’s test. Descriptive statistics will be used. Furthermore, the Friedman test will be used for analysis of repeated measurements. The False Discovery Rate (FDR) method will be applied to correct for the multiple testing problem. In the FDR method, every *p*-value is compared against a sequentially weighted threshold on all *p*-values [65].

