### Sample size calculation

#### Single-case data

The sample size needed for the abovementioned statistical analyses is different for the SCED and single-armed prospective study design. For the SCED design, the minimum sample size is *n* = 1. Instead, the power of the analysis depends on the number of observations [40, 41]. For randomization tests the lowest attainable *p*-value is calculated by dividing 1 by the number of possible permutations. In this study, the baseline phase, after removing the first four values because of a learning effect, can contain 5 to 24 measurement points, allowing 20 possible permutations. This corresponds with a lowest attainable *p*-value of 0.05 [56]. Of note, successful replication of the single-case experiment in additional participants with similar symptoms will improve the generalizability of the results [40, 41].

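### The primary A-versus-B hypothesis is tested one participant at a time with a p-value floor of 1/16, and the article states no trial-level test over the 15 replications

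*Protocol article*

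**What the plan says.** The Randomization test section states that "randomization tests will be performed to test the null hypothesis that NMES does not have an effect on" a participant's cognitive function. The difference between the phase A and phase B means "will be chosen as the primary outcome of this study". Two comparisons are planned: "The observations of the baseline phase will be compared to those of the intervention and follow-up phases respectively". If the plots suggest a delayed effect, "the randomization test will be repeated with lagged data until the lowest p-value has been reached".

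On replication, Study design says: "Replication of the experiment will be done in 15 participants". Effect sizes (NAP) are computed per participant. Consistency across participants appears only as one of the features examined under Visual analysis.

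On power, Sample size calculation (Single-case data) gives a minimum sample of one participant and continues: "Instead, the power of the analysis depends on the number of observations". Study design likewise ties power to data points and not to the number of participants. Replication is credited with improving generalizability. The same sample size section derives a lowest attainable p-value of 0.05 from 20 permutations.

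The one multiplicity provision is under Secondary statistics: "The False Discovery Rate (FDR) method will be applied to correct for the multiple testing problem". It concerns BDNF and the oral test battery. The figure of 15 participants comes from the secondary repeated-measures calculation, which gave a minimum of 7 and was then raised.

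**The concern.** The Introduction states a general hypothesis: that NMES benefits cognitive performance from the first weeks. The primary analysis yields 15 separate p-values, with no stated alpha, no combined p-value and no rule for how many participants must be positive. A reader of the results would have to decide afterwards what a mixed set of p-values means.

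Both directions carry risk. If NMES does nothing, some participants may still show the most extreme p-value that the design allows, and this can be taken as evidence of responders. If NMES helps everyone moderately, most individual tests may still miss that value, and this can be taken as inconsistency.

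The power rationale adds to the problem. In a test that re-draws one start point, the number of admissible starts fixes the p-value floor, and more intervention-phase observations do not lower it. The 15 starts are drawn independently, so they could support one valid trial-level test, but the article does not use them that way.

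**Working it through.** **1. The article's own figure.** Floor = 1 / number of possible starts. Sample size calculation uses a baseline of 5 to 24 points: 24 − 5 + 1 = 20 and 1/20 = 0.05. The figure reproduces, but only from that range.

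**2. The same figure from the other sections.**
- Study design, start drawn from 9 to 24: 24 − 9 + 1 = 16.
- Randomization test, 5 to 20 points left after the first four are dropped: 20 − 5 + 1 = 16.
- Both give 1/16 = 0.0625. Dropping four points moves both ends of the window (9 − 4 = 5, 24 − 4 = 20). The range 5 to 24 moves only the lower end.

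**3. What 15 separate tests deliver.**
- Read at 0.05 with 16 starts: the chance that an unlagged A-versus-B test reaches 0.05 is 0 for every participant, whatever the effect.
- Floor read as positive: 1 − (15/16)^15 = 0.620 for at least one positive among 15 null participants. For at least 3 it is 0.063, and for at least 4 it is 0.012.
- Bonferroni is no remedy: 0.05/15 = 0.0033, far below 1/16.

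**4. One combined test.** Under no effect, each p-value is taken as uniform on 1/16, 2/16, …, 16/16. The sum of 15 has mean 15 × 17/32 = 7.97. By exact convolution, the largest critical value with size at most 0.05 is 6.0625, with size 0.0465 (one-sided).

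**5. Power by simulation.** Inputs from the article: starts uniform on 9 to 24, first four points dropped, 36 intervention points, mean-difference statistic. Assumptions that are not in the article for this endpoint: an immediate constant shift of 0.5 or 0.71 within-person SD (0.71 is the effect size that the article borrows for the secondary endpoint), lag-1 autocorrelation of 0 or 0.3, and learning of 0 or 0.3 SD per log session. Each range below runs over the two autocorrelations.

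| Shift (SD) | Learning | One participant reaches 1/16 | Combined test, 15 participants |
|---|---|---|---|
| 0.5 | 0.3 | 13–14% | 52–66% |
| 0.5 | none | 13–15% | 55–71% |
| 0.71 | 0.3 | 17–18% | 77–88% |
| 0.71 | none | 17–19% | 80–92% |

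Under no effect, one participant reached the floor about 6% of the time and the combined test rejected in about 4–5% of simulated trials. For a shift of 0.5 SD without learning, combining only 7 participants gave 32–40% power. Replication therefore does add power once the p-values are combined.

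**The case against.** Participant-level inference is what this design declares. The study calls itself explorative, aims at individual effect courses, and gives replication a generalizability role. It never claims that replication adds power, and it does examine consistency across participants, if only visually. A family-wise rate over 15 individual nulls matters only if a trial-level claim is drawn from any single positive, and no section states such a rule. A condensed article may also leave a pooling rule to a fuller document that is not shown. All of this stands, and it limits the severity.

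A reader might go further and take 0.05 as the per-test alpha, concluding that the plan carries a 1 − 0.95^15 = 54% chance of a false positive. The article does not support that. It states no alpha for the primary test; its 0.05 is a claimed p-value floor. With 16 starts an unlagged test cannot reach 0.05, so the rate at that threshold is 0. The 62% also applies only if 0.0625 were called positive, which no section does.

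The sample size section does link the floor to the number of permutations, so that limit was not overlooked; it was miscounted. The power figures are conditional on assumptions, and a delayed effect, which the plan allows for, would change them.

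What the objection does not remove is that the article goes beyond silence. It takes the position that the number of participants is irrelevant to power, and it rests that position on a floor that its own start window does not give.

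**Conclusion.** The point holds as a recommended, cheap improvement, not as a must-fix. Followed as written, the plan gives no attainable 0.05 result in any single unlagged A-versus-B test (floor 0.0625 against the stated 0.05) and no test of its general hypothesis at a known error rate. The floor, the 62% and the combined size of 0.047 are exact if starts are uniform and independent and each null p-value is uniform on 16 values. The contrast between 13–19% for one participant and 52–92% for the combined test rests on the assumed shifts, autocorrelation and learning. It shows the order of magnitude and is not a forecast for this trial.

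A reader might infer that the individual tests are worthless or that the single-case design is invalid. Neither follows: the individual courses, plots and NAP still serve the exploratory aim.

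**What to change.** In Sample size calculation (Single-case data), correct the permutation count to 16 and the lowest attainable p-value to 0.0625, so that it agrees with Study design and Randomization test. Replace the statement built on a minimum of one participant with the power of the combined test at 15 participants, with its assumptions stated.

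In Randomization test, add one pre-specified trial-level A-versus-B test on the unlagged data. Two versions would serve:
- the sum of the 15 p-values, referred to its exact discrete null distribution; or
- the average of the 15 A-minus-B statistics, with starts permuted independently within participants.

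Name the outcome component and the direction. The smartphone test yields response time and accuracy ("speed, in ms) and the percentage of correct trials (accuracy"), and a one-sided test needs one of them fixed.

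Keep the individual p-values, visual analysis and NAP as exploratory participant-level results. Keep the lag-selected and A-versus-C p-values out of the confirmatory combination: a p-value chosen as the lowest over several lags is not uniform on 16 values, and the exact size would be lost.

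The cost is a few sentences and a few lines of code, with no new data, visits or participants. The downside is that individual responders are not declared from a single p-value. The rule must be fixed before the p-values are seen, because choosing it afterwards would forfeit its validity.
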